### Adverse event reporting and harms {22}

#### Adverse events (AEs)

Adverse events are defined as any untoward medical occurrence in a subject to whom a medicinal product is administered that does not necessarily have a causal relationship with this treatment. These AEs will be captured with CastorEDC, our electronic case report form (eCRF), as well as patient-reported outcome measures (PROMs) such as patient diaries and questionnaires.

#### Serious adverse events (SAEs)

A serious adverse event is any untoward medical occurrence or effect that results in death, is life threatening (at the time of the event), requires hospitalization or prolongation of hospitalization, results in persistent or significant disability or incapacity, or is a congenital anomaly or birth defect. Furthermore, an important medical event may be considered a Serious Adverse Event (SAE) when it potentially jeopardizes the subject. This determination is based on appropriate medical judgment and may require medical or surgical intervention to prevent serious outcomes.

To account for complications that are specific to the cancer treatment offered to our patients, and differentiate these, we defined context-specific serious adverse events as SAEs that are known complications of the disease, treatment or study intervention.

#### Suspected unexpected serious adverse reactions (SUSARs)

Adverse reactions are SUSARs if the following three conditions are met. First, the event must be serious. Second, there must be a certain degree of probability that the event is a harmful and undesirable reaction to the medicinal product under investigation, regardless of the administered dose. Last, the adverse reaction must be unexpected; that is to say, the nature and severity of the adverse reaction are not in agreement with the product information.

#### Reporting of AEs

Esophageal surgery is associated with considerable morbidity and mortality; therefore, numerous AEs and SAEs will occur within our study. It is clear that reporting all AEs has no added value and will not enhance patients’ safety. Therefore, we agreed to only note in the eCRF the AEs listed in the ECCG consensus on complications of esophageal resection from Clavien-Dindo score 3 onwards. AEs not documented in the above-mentioned ECCG list will be entered in the eCRF regardless of Clavien-Dindo score.

#### Reporting of SAEs/SUSARs by the investigator to the sponsor

The context-specific serious adverse events need to be reported in the AE section in the eCRF within 72 h after becoming aware (to avoid an incomplete annual safety report). If there occur SAEs/SUSARs that cannot be reasonably expected from the surgical intervention, study intervention or the disease for which the surgical intervention is planned, the investigator will report to the sponsor within 24 h.

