#### Secondary outcomes

Secondary endpoints include the incidence of postoperative complications, such as anastomotic leakage based on Esophageal Complications Consensus Group (ECCG) criteria, and the rate of reoperation within 30 days following surgery [21]. Complications will be graded according to the modified Clavien-Dindo classification [22]. Other secondary endpoints are postoperative length of stay in the hospital and the intensive care unit (ICU), as well as readmissions within 6 months after surgery, mortality, quality of life (QoL), direct and indirect costs, medication adherence, and side effects.

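### ECCG-listed events below Clavien-Dindo 3 that meet an SAE criterion are kept out of the eCRF by one safety rule and required in its AE section by another

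*Protocol article*

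**What the plan says.** Four statements matter, all within Adverse event reporting and harms {22}.

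- **What is serious.** Under Serious adverse events (SAEs), an event qualifies if, among other criteria, it "requires hospitalization or prolongation of hospitalization". No Clavien-Dindo grade is attached.
- **What is context-specific.** The same section continues: "we defined context-specific serious adverse events as SAEs that are known complications of the disease, treatment or study intervention". Again no grade is attached.
- **The AE rule.** Reporting of AEs starts from the expectation that "numerous AEs and SAEs will occur within our study". It concludes that sites will "only note in the eCRF the AEs listed in the ECCG consensus on complications of esophageal resection from Clavien-Dindo score 3 onwards". Events off that list are treated differently: "AEs not documented in the above-mentioned ECCG list will be entered in the eCRF regardless of Clavien-Dindo score".
- **The SAE rule.** Reporting of SAEs/SUSARs by the investigator to the sponsor says: "The context-specific serious adverse events need to be reported in the AE section in the eCRF". The limit is 72 h, and the stated reason is that the annual safety report would otherwise be incomplete. A separate 24 h route to the sponsor covers "SAEs/SUSARs that cannot be reasonably expected from the surgical intervention, study intervention or the disease".

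**The concern.** The AE rule filters ECCG-listed events by grade, whereas the SAE rule selects events by seriousness. The two scales differ: Clavien-Dindo grades a complication, while the SAE criteria include its effect on the hospital stay. The Background and rationale {6a} section itself says that pneumonia and anastomotic leakage lengthen hospitalization, which is one of the SAE criteria whatever the grade. A complication can therefore sit below the grade filter and still be serious.

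For such an event a site has two instructions with opposite results. A site that follows the AE rule makes no AE-section entry, and the annual safety report lacks an event that the SAE rule says it needs. A site that follows the SAE rule makes the entry. If sites differ in their choice, SAE counts are not comparable across hospitals. Evaluating the risks of SDD is among the secondary objectives, and the SAE record is one of its sources.

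**Working it through.** The protocol states no figure on this point and none can be recomputed. The check is whether any event falls under both rules with opposite results, and whether another provision resolves it.

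**Step 1. Cross the two classifications.**

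| Event | AE rule | SAE rule | Result |
|---|---|---|---|
| ECCG-listed, grade 3 or above, serious | record | record in AE section, 72 h | consistent |
| ECCG-listed, below grade 3, not serious | do not record | does not apply | consistent |
| ECCG-listed, below grade 3, serious, known complication | do not record | record in AE section, 72 h | **conflict** |
| Not ECCG-listed, any grade | record | record if a context-specific SAE | consistent |

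The conflict is confined to the third row.

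**Step 2. Can the third row occur?** Yes, under the protocol's own definitions. Neither the SAE definition nor the context-specific definition sets a minimum grade, and prolonged hospitalization is sufficient.

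**Step 3. Is there an exception for serious events in the AE rule?** None is written. The section Adverse events (AEs) defines an AE as any untoward medical occurrence, so every SAE is also an AE. The AE rule's rationale names SAEs alongside AEs.

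**Step 4. Do the two rules concern different forms?** No. The AE rule speaks of the eCRF as a whole, and the SAE rule names the AE section of that eCRF. Reading the filter as limited to the AE section leaves the conflict in place.

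**Step 5. Does another reporting route catch the event?**
- The 24 h route is for events that are not reasonably expected. A known complication is expected, so it does not qualify.
- Table 1 lists (S)AE assessment from D-3 to D180, but its footnote refers back to this same harms section and adds no rule.
- Under Secondary outcomes, "Complications will be graded according to the modified Clavien-Dindo classification", with no lower grade limit. Plans for assessment and collection of outcomes {18a} brings endpoint data into the eCRF. The event may therefore be in the database as an endpoint, but that is not the 72 h AE-section entry which the SAE rule links to the annual safety report.

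**The case against.** The best counter-reading is that the headings divide the work. Reporting of AEs would govern non-serious events only, and the next section would govern serious ones. On this view the AE rule mentions both classes, then restricts only AEs, and the more specific SAE rule prevails. This may well be what was intended. It is not stated, however. The AE definition includes SAEs, and the expected volume of SAEs is part of the reason given for the filter. If the reading is right, one sentence confirms it.

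Three further objections stand and limit the point.

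- **A reader might infer that all lower-grade ECCG-listed events vanish from the eCRF.** The protocol does not support that. Complications are a graded secondary endpoint, assessed at D30, D90 and D180. Length of stay and readmissions are collected. Pneumonia is the primary outcome, is checked by the monitor against all patients' medical records, and goes to an adjudication committee. What may be missing is the AE-section entry.
- **A reader might infer a distorted comparison of SAE rates between arms.** This is not shown. Randomization is stratified by hospital, so a site's habitual reading of the rules would apply to both arms. The trial is open-label, so staff who choose between the rules know the allocation, but nothing in the document shows that they would choose differently by arm.
- **A reader might infer that the risk evaluation as a whole fails.** It has other sources: DSMB access to primary and secondary endpoint data and its review of causes of death, diaries and questionnaires, off-list events at any grade, and the 24 h route.

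It can also be said that a journal article condenses the full protocol, and that eCRF instructions not shown may settle the matter. That would excuse a missing detail. Here both rules are printed and give opposite instructions. Whether sites have in fact diverged is unknown.

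**Conclusion.** The point holds in a limited form. As printed, an ECCG-listed complication below Clavien-Dindo 3 that meets an SAE criterion is both excluded and required, and it can be missing from the AE section and the annual safety report even when it is recorded as an endpoint.

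The size cannot be given. It is tempting to start from the expected pneumonias under the sample-size assumptions: 427 × 0.22 + 427 × 0.13 = 93.9 + 55.5, or about 149. One would then apply a share that stays below grade 3 and prolongs the stay. The document gives no such share and does not reproduce the ECCG list, so the result would be only the assumption restated. Pneumonia is also the event least likely to be lost.

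The conclusion rests on the printed wording of the three harms subsections and on the absence of any stated exception. It does not depend on a count. It is worth correcting because the rule as written can remove safety reports that the protocol itself requires, and the correction is small.

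**What to change.** Reconcile Serious adverse events (SAEs), Reporting of AEs, and Reporting of SAEs/SUSARs by the investigator to the sponsor. In Reporting of AEs, state that the Clavien-Dindo 3 filter applies only to ECCG-listed AEs that meet no SAE criterion. An ECCG-listed event that does meet one is entered in the AE section within 72 h whatever its grade, as the SAE rule already says. Carry the same sentence into the eCRF completion instructions and apply it identically at all sites and in both arms.

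The cost is one sentence, a notice to sites, and some additional SAE entries, which the SAE rule already requires. Because recruitment began in October 2024, the sponsor should also ask sites which rule they have followed so far and complete any entries left out.

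### The 24 h investigator report uses a different expectedness test from the SUSAR definition, so a SUSAR that is also a known complication of the surgery or disease falls into the 72 h route

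*Protocol article*

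**What the plan says.** Four parts of the Protocol article's section on adverse event reporting and harms {22} bear on this point.

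- **SUSAR definition.** Three conditions apply: the event is serious, there is some probability that it is a reaction to the investigational product, and it is unexpected, meaning that "the nature and severity of the adverse reaction are not in agreement with the product information". Surgery and underlying disease play no part in the definition.
- **Context-specific SAEs** (under Serious adverse events). These are defined as "SAEs that are known complications of the disease, treatment or study intervention". No exception is made for an event suspected to be a reaction to SDD.
- **Reporting by the investigator to the sponsor.** Context-specific SAEs "need to be reported in the AE section in the eCRF within 72 h after becoming aware", and the reason given is "to avoid an incomplete annual safety report". A faster report, due in 24 h, is reserved for "SAEs/SUSARs that cannot be reasonably expected from the surgical intervention, study intervention or the disease".
- **Reporting to EudraVigilance.** The sponsor must report SUSARs within 7 days if fatal or life-threatening and within 15 days otherwise, counted from the sponsor's awareness. This duty carries no filter for surgery or disease.

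**The concern.** Two rules sort the same events by different yardsticks. The definition asks whether the product information already describes the reaction. The 24 h rule asks whether surgery, SDD or the disease could account for the event, and it applies that filter to SUSARs by name. Suspected causality to SDD, which is central to the definition, is not part of the 24 h test.

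The two tests part company where a drug reaction and surgical morbidity look alike. The article itself expects numerous AEs and SAEs after this operation, and its Discussion says that the large SDD safety and efficacy studies did not include esophageal patients. Evaluating the risks of SDD is a secondary objective. At stake is how quickly a suspected, undescribed serious reaction reaches the sponsor, and whether it is seen as a SUSAR when it arrives. No treatment-effect estimate or error rate is affected.

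**Working it through.** The main check is one of logic, since the plan gives no figure to reproduce.

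**Inputs.** From the SUSAR definition: serious, suspected relation to SDD, not in agreement with the product information. From the investigator-to-sponsor section: the 24 h route requires that the event be unexpected from surgery *and* from SDD *and* from the disease, so one alternative explanation is enough to remove it. From the SAE section: a known complication of any of the three is context-specific and takes the 72 h route.

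**Serious events run through both rules:**

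| Suspected due to SDD | Agrees with product information | Known complication of surgery or disease | SUSAR by definition | Route as written | Conflict |
|---|---|---|---|---|---|
| Yes | No | No | Yes | 24 h | No |
| Yes | No | Yes | Yes | 72 h, eCRF | **Yes** |
| Yes | Yes | Either | No | 72 h, eCRF | No |
| No | – | Yes | No | 72 h, eCRF | No |
| No | – | No | No | 24 h | No |

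The first row assumes that an event outside the product information is also not regarded as a known complication of SDD; the third assumes the reverse. On that basis only the second row conflicts. Naming the study intervention in the filter does not help there, because the event is already removed by being expected from the surgery or the disease.

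**Delay at the investigator-to-sponsor step.** The article starts the 72 h clock at awareness. It gives no start for the 24 h clock, so awareness is assumed there too.

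- Maximum delay: 72 h − 24 h = 48 h.

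**Effect on the outer limit for EudraVigilance.** Assume further that the sponsor becomes aware when the report or the eCRF entry is made, and recognises the event as a SUSAR at that moment.

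- Fatal or life-threatening: 1 + 7 = 8 days from investigator awareness by the 24 h route, against 3 + 7 = 10 days by the 72 h route.
- Other: 1 + 15 = 16 days, against 3 + 15 = 18 days.

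If the entry is not recognised as a SUSAR, the text sets no outer limit, because the sponsor's clock runs from awareness of the reaction.

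**The case against.** The strongest reply is that nothing in the text releases the sponsor from reporting. The EudraVigilance section covers every SUSAR, the event must still be in the eCRF within 72 h, and the DSMB reviews the cause of every death for a possible relation to the study intervention. This stands. A reader might infer that SUSARs resembling surgical complications escape expedited reporting altogether. The documents do not support that: what they establish is loss of the 24 h step, and a missed report is only a risk. The safeguards are partial all the same. The DSMB's stated causality review concerns deaths only, and the sponsor's clock depends on recognising a reaction in a stream described as serving the annual report.

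Three other inferences also fail.

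- *That every suspected serious reaction to SDD is affected.* Reactions in agreement with the product information are not SUSARs, so for them the rules do not conflict.
- *That the expected pneumonias and anastomotic leaks show the scale.* They count complications in both arms, and control patients receive no SDD. They do not count suspected unexpected reactions.
- *That the renal and neuromuscular exclusion criteria reveal likely SDD toxicity of this kind.* The article gives no reason for those exclusions and calls the agents non-absorbable. If they do reflect known risks, such events may already be in the product information, which is not shown.

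Finally, this is a condensed article, and the full protocol may contain a causality assessment and SAE forms. Their absence here is therefore no finding. The point rests on two rules that the article does state and that give different answers for the same event.

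**Conclusion.** The point holds in a narrow form. For a serious event that is suspected to be due to SDD, is not in agreement with the product information and is also a known complication of esophagectomy or the disease, the article's SUSAR definition and its investigator reporting rule contradict each other. The established consequence is that the event leaves the 24 h route and may reach the sponsor up to 48 h later, assuming both clocks start at investigator awareness. Failure to recognise it for the 7- or 15-day report is possible but not certain. How many events are affected cannot be estimated from the article, and the number may be very small. The case for correction is that the contradiction is plain, concerns participant safety and is cheap to remove.

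**What to change.** Reconcile the SAE definition, the SUSAR definition and the investigator-to-sponsor section so that they use one basis:

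1. Any SAE that may meet the SUSAR definition, that is, with a suspected relation to SDD and not in agreement with the product information, goes to the sponsor by the 24 h route, whether or not it is also a known complication of the surgery or the disease.
2. The context-specific class, and with it the 72 h eCRF route, expressly excludes such events.

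This needs a few sentences of protocol wording and brings a small number of extra 24 h reports. Treatment, sample size and analysis are unchanged. If the full protocol already routes these events this way, correcting the article's wording is enough.

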#### Reporting of SUSARs to the EUDRAVigilance database

The sponsor takes responsibility for the electronic reporting of SUSARs in EUDRAVigilance without delay. The period for the reporting of SUSARs to the EMA by EUDRAVigilance will take into account the seriousness of the reaction and will be as follows: First, in the case of fatal or life-threatening SUSARs, as soon as possible and in any event not later than 7 days after the sponsor became aware of the reaction. Second, in the case of non-fatal or non-life-threatening SUSARs, not later than 15 days after the sponsor became aware of the reaction. Third, in the case of a SUSAR that was initially considered to be non-fatal or non-life threatening but which turns out to be fatal or life-threatening, as soon as possible and in any event not later than 7 days after the sponsor became aware of the reaction being fatal or life-threatening. Where necessary to ensure timely reporting, the sponsor may, in accordance with section 2.4 of Annex III, submit an initial incomplete report followed up by a complete report (CTR: Article 42 [2]).

### Frequency and plans for auditing trial conduct {23}

At any given point during the study, the trial can be selected for audit. There is no predefined schedule for audits and inspections.

### Plans for communicating important protocol amendments to relevant parties (e.g., trial participants, ethical committees) {25}

If any substantial modifications to the original documents are made we will submit these via CTIS. After approval the DSMB, Monitor, Trial Steering Committee, and the local principal investigators will be notified. If necessary updated documents will be provided for the participating hospitals and adjusted on the trial website.

### Dissemination plans {31a}

The results of the PERSuaDER trial will be fully disclosed through publication in a peer-reviewed journal and through presentations at national and international scientific conferences.

## Discussion

Esophagectomies are often followed by (infectious) complications, especially pneumonia. To reduce the risk of pneumonia, some hospitals in the Netherlands already use SDD. However, the scientific evidence remains limited. The large studies demonstrating the safety and efficacy of SDD in reducing infectious complications and mortality were never conducted in esophageal patients. These trials primarily involved patients in intensive care units or those undergoing elective (mostly lower) gastrointestinal surgery [14, 29, 30]. To date, little evidence exists regarding the perioperative use of SDD in esophageal cancer surgery. The few studies addressing this population are generally observational, vary in SDD composition and duration and are often small or of lower quality.

We designed a large, open-label randomized controlled trial comparing standard care with SDD to standard care without SDD, to find the much-needed evidence on the efficacy of SDD in patients undergoing esophageal cancer surgery. We selected the most widely used SDD formulation, combining amphotericin-B, colistin and tobramycin to target not only the most common bacterial pathogens, namely gram-negative rods, but also yeasts. Our study does have some limitations. A key point to consider is that no placebo will be used in our trial. Patients receiving SDD in addition to standard care will be compared to a control group receiving standard care without a placebo. Incorporating a placebo in this large, investigator-initiated drug trial was deemed impractical, as a significant portion of the intervention occurs at home without study staff supervision. This design reflects a real-life scenario, in contrast to the potential selection bias that may arise in placebo-controlled trials. However, the absence of a placebo increases the risk of biased outcome assessment. To mitigate this, we have implemented objective criteria for the primary endpoint. Furthermore, global shortages of SDD components may require adjustments to the composition of our investigational medicinal product (IMP). However, a suitable alternative is available, and such modifications also occur in clinical practice. Therefore, the intervention remains well-defined and reflective of real-world conditions, making the intervention sufficiently well-defined.

The PERSuaDER-trial aims to provide a robust and prospective evaluation of perioperative SDD as a protective strategy to reduce postoperative pneumonia in esophageal cancer surgery. The results of this trial could play a crucial role in guiding the decision-making process regarding the implementation of this off-patent, widely available prophylactic strategy, potentially resulting in significant health benefits and a substantial reduction in healthcare costs.

